## Abstract

**Background:**

Biomass fuel is used as a primary cooking source by more than half of the world’s population, contributing to a high burden of disease. Although cleaner fuels are available, some households continue using solid fuels because of financial constraints and absence of infrastructure, especially in non-notified slums. The present study documents a randomised controlled study investigating the efficacy of improved cookstove on the personal exposure to air pollution and the respiratory health of women and children in an Indian slum. The improved cookstove was based on co-creation of a low-smoke chulha with local communities in order to support adaption and sustained uptake.

**Methods:**

The study will be conducted in a non-notified slum called Ashrayanagar in Bangalore, India. The study design will be a 1:1 randomised controlled intervention trial, including 250 households. The intervention group will receive an improved cookstove (low-smoke chulha) and the control group will continue using either the traditional cookstove (chulha) or a combination of the traditional stove and the kerosene/diesel stove. Follow-up time is 1 year. Outcomes include change in lung function (FEV_1/_FVC), incidence of pneumonia, change in personal PM_2.5_ and CO exposure, incidence of respiratory symptoms (cough, phlegm, wheeze and shortness of breath), prevalence of other related symptoms (headache and burning eyes), change in behaviour and adoption of the stove. Ethical clearance was obtained from the Institutional Ethics Committee of the Indian Institute of Public Health Hyderabad- Bengaluru Campus.

**Discussion:**

The findings from this study aim to provide insight into the effects of improved cookstoves in urban slums. Results can give evidence for the decrease of indoor air pollution and the improvement of respiratory health for children and women.

**Trial registration:**

The trial was registered with clinicaltrials.gov on 21 June 2016 with the identifier NCT02821650; A Study to Test the Impact of an Improved Chulha on the Respiratory Health of Women and Children in Indian Slums.

**Electronic supplementary material:**

The online version of this article (doi:10.1186/s12889-017-4369-6) contains supplementary material, which is available to authorized users.

## Background

Biomass fuel is used as a primary cooking source by more than half of the world’s population [1, 2]. About three-fourths of this practice occurs in developing countries [1, 3]. Indoor air pollution (IAP) from the use of biomass fuel results in a high burden of morbidity and mortality globally, disproportionately affecting low- and middle-income countries [1, 4]. Exposure is particularly high among women and young children who spend most of their time near the fire [5, 6]. IAP doubles the risk for pneumonia and other respiratory infections for children under the age of 5 years [7]. In addition to respiratory problems, IAP has been linked to tuberculosis, cataracts, preeclampsia/eclampsia, infant mortality, low birth weight and preterm birth [5, 8]. An estimated 70% of Indian households make use of solid fuels [9, 10]. IAP contributes to 4.2% and 6.1% of total morbidity in India, affecting mainly women and children [11]. Although cleaner fuels are available, some groups continue using solid fuels because of financial constraints and absence of infrastructure, especially in non-notified slums [12]. In the short-term, improving cookstoves are often the only affordable solution to reduce IAP [1, 2]. The current EXHALE study initiated by Maastricht University, Zuyd University of Applied Sciences, Indian Institute of Public Health Bangalore, in close collaboration with Narayana Health Hospital and Baptist Hospital located in Bangalore.

## Aims

The aim of the present trial is to reduce the levels of household air pollution and improve the respiratory health of women and children by using a locally designed and manufactured improved cook stove. The study design will be a 1:1 randomised controlled intervention trial.

## Methods

### Study setting

The study area is a non-notified slum called Ashrayanagar in Bangalore, India. This slum is located within 8–12 km from the center of Bangalore. No official record exists on the date of origin of the slum, area covered by the slum, and number of inhabitants. The slum is dynamic in its composition, ranging from concrete houses to basic sheet houses, separated by narrow streets. There are an estimated 1100 households. Most of the households typically cook on traditional three-stone fires (chulha) or kerosene stoves.

### Eligibility criteria

Woman ≥18 years who cooked more than 50% of the meals during the past 30 days (primary cook) and one child per household (0–5 years) will be included in the study. Both households with and without children will be included. When there is more than one child in the age group 0–5 years in a household, one child will be randomly chosen. Women should be capable of being interviewed, and should not migrate in the upcoming 2 months as far as they can predict. Only households cooking solely with a traditional cookstove (chulha) or a combination of a traditional stove and a kerosene/diesel stove will be included. Households with a cooking area outside the house will be excluded. Persons who are seriously ill will be excluded from the study.

### Intervention

The intervention group will receive a locally designed and manufactured improved cookstove (low-smoke chulha). The control group will continue using the traditional cookstove (chulha) or a combination of the traditional stove and the kerosene/diesel stove. The new chulha consists of a primary burner, a secondary burner, a chimney chamber, and a chimney. The improved cookstoves will be installed by field workers. If the stove needs repair during the study, fieldworkers will take care of it.

The first part of project EXHALE was based upon an iterative process of co-creation of a low-smoke chulha with local communities in order to support adaption and sustained uptake. A qualitative study was conducted to gain insight into the cooking practices and challenges faced with the traditional stoves [12]. Workshops were conducted where people were involved in creating an ideal stove, using thermocol blocks. Feedback was continuously used to optimize the design of the cookstove [12]. Improved cookstoves were evaluated in a qualitative study in a slum called Siddhaarthanagar colony in Bangalore. Results of this study will be published elsewhere.

### Outcomes

The primary outcomes include (1) change in lung function (FEV_1_/FVC) over a period of 1 year as measured by spirometry in the primary cook and (2) incidence of pneumonia over the period of 1 year for children ≤5 years. Secondary outcomes include (1) change in personal PM_2.5_ and CO exposure over a period of 1 year for the primary cook (2) incidence of respiratory symptoms, including cough, phlegm, wheeze and shortness of breath over a period of 1 year for the primary cook (3) prevalence of other related symptoms, including headache and burning eyes over a period of 1 year for the primary cook and (4) change in behaviour and attitudes of user and adoption of the improved cookstove over a period of 1 year as part of a process evaluation.

Primary outcomes, including lung function and pneumonia, were selected based on their prevalence in the specific age-groups. Pneumonia is the leading infectious cause of death in children aged 0–5 years and a substantial part might be attributable to IAP [13]. Lung function will be measured to quantitatively assess the relationship between biomass fuel use and lung function impairment.

### Participant timeline

The follow-up time of the study is 1 year (Fig. 1 and Table 1).

**Fig. 1 Fig1:**
[figure not shown]
Trial flow-chart

**Table 1 Tab1:** Overview measurements

	FEV_1_/FVC	Pneumonia	Personal PM_2.5_ and CO exposure	Respiratory symptoms	Other related symptoms	Behaviour, attitude and adoption
Baseline (May – July 2017)	X	X	X	X	X	
3 months		X		X	X	
6 months	X	X	X	X	X	X
9 months		X		X	X	
12 months	X	X	X	X	X	X

### Sample size

For adult women, the primary outcome is the mean change in FEV_1_/FVC after 12 months compared to baseline. Based on previous research [14], a standardized effect size of 0.562 is expected, which is a medium to large effect size [15]. To detect this effect size with 80% power and a significance level α of 0.05, 51 adults per group (intervention or control) are required. To account for 25% dropout, the required number of adults is equal to 68 per group. As for children younger than or equal to 5 years, the primary outcome is the proportion of children with pneumonia during the study (within 12 months). Assuming a dropout rate of 25% [16], and a proportion (incidence) of 0.50 within the control group [17], 124 children aged 5 or younger within each group (intervention or control) are required to detect a clinically relevant difference in proportions of 0.20 (proportion of 0.30 in intervention group) with 80% power and a significance level α of 0.05. Therefore, a total of at least 250 households with at least one child aged 5 years or younger will be selected in this study. Next to the child aged 5 years or younger (or the randomly selected child aged 5 or younger if there is more than one eligible child), the adult who is responsible for cooking (mother or someone else) will also be asked to participate. This will ensure that the sample size is also large enough for the adults group (see sample size calculation above). Both eligible households with and without children will be included. The study will be extended to other slums, in case the sample size could not be met in Ashrayanagar slum.

### Recruitment

All houses in the slum area will be mapped manually to create an overview of the study area. Local leaders will be informed about the study and community meetings will be organized. Eligible households will be identified based on inclusion and exclusion criteria. Eligible households will be asked to participate and will be informed about the study procedure. To maximise retention, all households, including the control group, will be informed that they receive the intervention at the end of the study period. Households willing to participate will be asked to sign an informed consent form. In case of children, informed consent will be obtained from mothers or caregivers. Due to high levels of illiteracy common in the slum, an independent witness will be present if eligible participants are illiterate when signing the form.

### Randomisation

Block randomisation will be performed to reduce bias and achieve balance in the allocation of participants to treatment arms [18]. Block sizes vary between two, four and six households to reduce the possibility of knowing the next randomisation allocation. A field team will recruit households. All households participating will receive an ID number, which is given to a non-field member who records the randomisation allocation assigning them to either the intervention or control group. The study will be single-blinded (data-analyst). Randomisation is stratified for having a child aged 5 years or younger or not. A primary cook with a child aged 5 years or younger will be randomised according to the randomisation of the child. Primary cooks without a child aged 5 years or younger will be additionally randomised.

### Data collection

#### Lung function

Change in lung function (FEV_1/_FVC) will be assessed over a period of 1 year as measured by spirometry in the primary cook. Spirometry would be done thrice; at baseline, at 6 months and after 1 year of intervention. Spirometry will be carried out by trained fieldworkers. The highest outcome of three attempts at each point in time will be used in data analysis. A Spirodoc spirometer (MIR, Italy) will be used to assess lung function.

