### Data management

Data for the questionnaires and for the assessment of pneumonia will be collected using a tablet computer with a pre-formatted questionnaire sheet. Data will directly be transferred to an online cloud. The system uses 128-bit SSL secured layer for all data transactions. Both the software subsystem and the database system are secured by this layer. The system can only be accessed through secured username and password. The principle of least privilege, whereby access will be limited to the minimal level that will allow normal functioning, will be followed. Interviews will be audio-recorded and a transcript will be made by fieldworkers after the visits. Data will be stored on a hard-drive. Personal air pollution measurements will be stored on an SD-card in the device and ambient air pollution measurements will be stored on an SD-card and in an online website. Results of spirometry will be transferred to the software winspiroPRO after every visit and will be stored on a hard-drive. Back-ups will be made for all measurements to avoid loss of data. All data collection and storage devices will be password protected. Identifiers, data, and keys will be placed in separate, password protected/encrypted files. Only supervisors and the main researcher will have access to the data files, identifiers, and keys. All data will be stripped of identifiers as soon as possible, and managed by use of a code.

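### As written, the spirometry rule takes the highest FEV1/FVC ratio of three attempts, which favours blows ended early and adds noise to the adult primary outcome

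*Protocol article*

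**What the plan says.** The Lung function section of the protocol article says that change in FEV1/FVC "will be assessed over a period of 1 year as measured by spirometry in the primary cook". No other lung-function outcome is named there. The section continues: "Spirometry would be done thrice; at baseline, at 6 months and after 1 year of intervention", "Spirometry will be carried out by trained fieldworkers", and then the selection rule: "The highest outcome of three attempts at each point in time will be used in data analysis".

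The Sample size section fixes the estimand as a change, not a level: "For adult women, the primary outcome is the mean change in FEV_1_/FVC after 12 months compared to baseline". It plans on the statement that "a standardized effect size of 0.562 is expected", which gives 51 adults per group, or 68 after 25% dropout. The children's calculation then sets the overall size at 250 households or more.

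Two further statements matter here. On blinding, the Randomisation section says "The study will be single-blinded (data-analyst"). On storage, the Data management section says "Results of spirometry will be transferred to the software winspiroPRO after every visit".

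**The concern.** Taking the maximum of several attempts is sensible for a volume, because a poor effort can only lower FEV1 or FVC. A ratio behaves differently. If the blow stops early, FEV1 may be intact while FVC, the denominator, is too small, and the ratio rises. For example, with a true ratio of 0.80 and an FVC that falls 10% short, the recorded ratio is 0.80 / 0.90 = 0.89. A rule that keeps the highest ratio will tend to keep such a blow in preference to a complete one.

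Two things are at stake. First, the recorded ratio depends more on how completely the woman exhaled that day, so the change score carries more measurement error and the planned standardised effect may not be reached. Second, the outcome becomes more sensitive to coaching. The operators are fieldworkers who are not stated to be blinded, so coaching could differ between arms.

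**Working it through.** **1. The plan's own figure.** For two means with two-sided α = 0.05 and 80% power, n per group = 2(1.960 + 0.842)² / 0.562² = 49.7, so 50. The t-based version gives 50.7, so 51. Allowing for dropout, 51 / 0.75 = 68. Both stated figures reproduce, and the sample-size arithmetic is not in question.

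**2. Adults actually expected.** 250 households at 1:1 give 125 primary cooks per arm, and 125 × 0.75 = 93.75, so about 93 completers. At d = 0.562, power is about 80% with 51 per arm and about 97% with 93.

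**3. Effect of the rule on measurement error.** The documents give no within-session variation, so these inputs are assumptions: true ratio 0.82, FVC shortfall per attempt exponential with mean 2–3%, and FEV1 shortfall half-normal with SD 2%. Three attempts per visit were simulated and two rules compared.

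| Rule | Shift in level | Error SD of one visit's ratio |
|---|---|---|
| Highest ratio | about +0.02 to +0.04 | 0.021 to 0.034 |
| Largest FEV1 / largest FVC | 0.000 to about +0.003 | 0.007 to 0.010 |

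Under the highest-ratio rule, the attempt kept was the one with the lowest FVC in about 76–82% of cases.

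**4. Effect on the change score.** Assume that the SD of the 12-month change is 0.04 under the second rule and that 0.562 applies to that rule. Replacing the error term at both visits gives

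SD(change, highest ratio) = √(0.04² − 2e_best² + 2e_high²).

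- Mean shortfall 2%: √(0.0016 − 2 × 0.007² + 2 × 0.021²) = √0.002384 = 0.049, and d = 0.562 × 0.04 / 0.049 = 0.46.
- Mean shortfall 3%: √(0.0016 − 2 × 0.010² + 2 × 0.034²) = √0.003712 = 0.061, and d = 0.562 × 0.04 / 0.061 = 0.37.

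**5. Effect on power.** At 93 per arm, d = 0.46 gives about 88% and d = 0.37 about 70%, against about 97%.

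**6. A different error model.** A second simulation assumed a half-normal 3% shortfall in both FEV1 and FVC, plus a share of blows ended early with 5–15% of FVC lost.

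| Share of blows ended early | 0% | 10% | 20% | 40% |
|---|---|---|---|---|
| Measurement SD of change, highest ratio (points) | 2.4 | 5.6 | 6.5 | 6.3 |
| Measurement SD of change, largest FEV1 / largest FVC (points) | 1.4 | 1.6 | 1.9 | 3.1 |

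With 10–40% short blows and a true-change SD of 3–7 points (assumed), d is about 0.28–0.46 and power at 93 per arm about 48–88%. The direction is the same and the range is wider.

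**7. Bias in the change.** In the second simulation the mean spurious change is 0.0 under both rules when the share of short blows is equal at the two visits. If that share falls from 40% to 10%, the spurious within-arm change is −4.3 points with the highest ratio and −0.8 with the alternative. If this happens equally in both arms, it cancels in the treatment comparison.

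**The case against.** The strongest reply is that the sentence is shorthand for the highest FEV1 and the highest FVC taken separately. That is possible, and most of the problem would then disappear. But the sentence does not say so, and the only outcome in its section is the ratio. Two analysts could derive different primary outcomes from the same records, so the sentence needs rewording on either reading.

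A reader might infer that the rule biases the adult primary outcome upward. The document does not support that. The outcome is a change compared between randomised arms, so a constant shift in level drops out, as does a learning or fatigue effect common to both arms. Bias in the treatment effect needs effort or coaching to differ by arm. The stated blinding leaves that open, but nothing shows that it will happen.

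A reader might also put the power loss at 51 adults per arm, where the same inputs give roughly 45–63%. That is the stand-alone adult requirement. The child-driven sample leaves about 93 completers per arm, and this margin absorbs much of the loss.

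Nor does the rule always pick the most incomplete exhalation. With no blows ended early, it picks favourable random error (+1.8 points in the second simulation) and is still less noisy than a single attempt (SD of change 2.4 against 3.0 points).

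Two further cautions stand. If the study behind 0.562 used the same selection rule, the extra noise is already in that figure. And the article's silence on which attempts count as acceptable is not itself a fault, since such detail is commonly left to the full protocol. Screening out short blows would reduce the effect.

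**Conclusion.** The point holds as a defect in a stated primary-outcome rule. Taken literally, the rule favours blows ended early, raises the level of FEV1/FVC and makes the 12-month change noisier than the largest FEV1 over the largest FVC. That mechanism follows from the ratio itself; its size does not follow from the documents.

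The best-supported statement of size is a fall in d from 0.562 to about 0.37–0.46, leaving power at about 93 completers per arm at about 70–88%. It rests on a mean FVC shortfall of 2–3%, an SD of change of 0.04, no screening of unacceptable attempts, 0.562 having come from the better rule, and a simple comparison of changes. Harsher inputs give lower power. Bias in the treatment effect is possible but conditional on differences between arms.

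**What to change.** Replace the selection sentence in the Lung function section by:

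> At each visit FEV1/FVC is the largest FEV1 divided by the largest FVC among the technically acceptable attempts, whether or not they come from the same attempt.

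Apply it identically at baseline, 6 months and 12 months, and settle it before any unblinded analysis. No new measurement is needed. The cost is one sentence and a recomputation from the stored spirometry records, provided that individual attempts are retained there, which the sponsor should confirm. The rule reduces sensitivity to effort but does not remove it.

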#### Pneumonia

The incidence of pneumonia for children ≤5 years will be determined according to the definition of the WHO Integrated Management of Childhood Illness (IMCI). Pneumonia is defined as cough or difficulty breathing and fast breathing (respiratory rate ≥ 60, ≥50 or ≥40 breaths per minute in those aged <2 months, 2–12 months and 1–5 years respectively). Severe pneumonia is defined as cough or difficulty breathing and chest-indrawing, stridor or any general danger signs. General danger signs include inability to drink or breastfeed, vomiting, convulsions, lethargy, or unconsciousness [19].

Screening for pneumonia will be done every 3 months for 1 year. Physical examination will be conducted by trained fieldworkers.

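### The 80% power for 12-month pneumonia (0.50 vs 0.30) does not match case-finding described as quarterly examination; unless episodes between visits are also recorded, power could be about 14% to 44%

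*Protocol article*

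**What the plan says.** The Outcomes section of the protocol article lists as the second primary outcome the "incidence of pneumonia over the period of 1 year for children ≤5 years". The Sample size section puts it as a cumulative proportion: "the primary outcome is the proportion of children with pneumonia during the study (within 12 months"). It assumes "a proportion (incidence) of 0.50 within the control group" and "a clinically relevant difference in proportions of 0.20 (proportion of 0.30 in intervention group"), allows for 25% dropout, and concludes that "124 children aged 5 or younger within each group (intervention or control) are required". This child calculation sets the trial at 250 households; the lung-function outcome needs only 68 women per group.

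On case-finding, the Pneumonia section says: "Screening for pneumonia will be done every 3 months for 1 year. Physical examination will be conducted by trained fieldworkers". Table 1 places pneumonia assessment at baseline and at months 3, 6, 9 and 12. The case definition has two branches. Pneumonia is cough or difficult breathing with an age-specific fast respiratory rate. Severe pneumonia is cough or difficult breathing with chest-indrawing, stridor or a general danger sign. The 3-monthly symptom questionnaire in the Questionnaires section is described for the primary cook, not the child. The article describes no visit triggered by a caregiver, no clinic or hospital record and no interval history for the child.

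**The concern.** A proportion affected within 12 months counts every child with at least one episode on any day of the year. Examinations on four post-baseline days count children who show signs on one of those days. The two agree only if an episode stays detectable for most of the gap between visits. If signs last days or weeks, most episodes fall between visits, both arms' observed proportions drop, and the absolute difference drops with them.

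The power statement takes the 12-month proportions as if they would be observed in full. If they are not, a null child result becomes likely even when the stove delivers the whole assumed benefit, and it could be read as evidence that the stove does not prevent pneumonia.

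**Working it through.** **1. The plan's own figure.** Inputs from the Sample size section: p1 = 0.50, p2 = 0.30, α = 0.05 (two-sided assumed), power 80%, dropout 25%. With pooled variance and no continuity correction:

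n = [1.96·√(2·0.40·0.60) + 0.842·√(0.25 + 0.21)]² / 0.20² = (1.358 + 0.571)² / 0.04 ≈ 93 per group.

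93 / 0.75 = 124, as stated. The arithmetic of the plan is right.

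**2. Turning 12-month risks into rates.** If 0.50 and 0.30 are true cumulative risks at a constant rate, then rate = −ln(1 − p):
- control: 0.693 per child-year
- intervention: 0.357 per child-year

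**3. What four examinations would detect.** Let signs be detectable for D days. D is an assumption. Prevalence on a visit day is about rate × D/365. Two simple formulas give the proportion positive at least once:
- (i) 1 − exp(−4 × rate × D/365)
- (ii) 1 − (1 − rate × D/365)⁴, which treats visits as independent

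**4. Power with 93 evaluable per arm**, ever/never comparison:

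Φ{ [|p1 − p2|·√93 − 1.96·√(2·p̄·(1 − p̄))] / √(p1(1 − p1) + p2(1 − p2)) }

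Example, D = 14, formula (i): p1 = 0.1009, p2 = 0.0533, p̄ = 0.0771. The numerator is 0.459 − 0.739 = −0.280 and the denominator 0.376, so Φ(−0.745) = 0.228.

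| D (assumed) | Control vs intervention, (i) | Power (i) | Control vs intervention, (ii) | Power (ii) |
|---|---|---|---|---|
| 7 days | 0.052 vs 0.027 | 14% | 0.052 vs 0.027 | 14% |
| 14 days | 0.101 vs 0.053 | 23% | 0.102 vs 0.054 | 23% |
| 30 days | 0.204 vs 0.111 | 41% | 0.209 vs 0.112 | 44% |
| 60 days | 0.366 vs 0.209 | 66% | 0.384 vs 0.215 | 71% |
| 75 days | 0.434 vs 0.254 | 74% | 0.459 vs 0.263 | 80% |
| 91.25 days | 0.500 vs 0.300 | 80% | 0.533 vs 0.312 | 87% |

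Power of 80% therefore returns at about 75 days under (ii) and 91 days under (i). Exact binomial enumeration under (i) gives 12%, 23% and 42% at 7, 14 and 30 days, so the normal approximation is not driving the result.

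**5. Cross-check.** For four independent visits to yield 0.50 and 0.30, the proportion meeting the definition on each visit day would have to be 1 − 0.5^(1/4) = 15.9% in control and 1 − 0.7^(1/4) = 8.5% in intervention.

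**6. Sensitivity.** Counting the baseline examination as a fifth look gives 16%, 27% and 49% at 7, 14 and 30 days under (i). A case found at baseline does not inform the effect of the stove in any event.

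**The case against.** The strongest objection is that the article does not say examination is the only source. It is a condensed account. The Data management section mentions a pre-formatted questionnaire sheet for assessing pneumonia, and Additional file 1, which holds the questionnaires, is not shown. Questions about illness since the last visit may be there. Nor does the case definition rule out history: some danger signs in the severe branch, such as vomiting, convulsions or inability to drink, can be reported by a caregiver. This stands, and it makes the point conditional. It does not remove it, because the non-severe branch depends on a counted respiratory rate, which recall cannot supply. If interval history can make a case, the definition should say so.

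The size of the loss also rests on unknowns. The article gives no duration of signs. The source of the 0.50 is not at hand; if it already reflects periodic screening, discounting it again would count the loss twice. Against that, the Sample size section calls the figure an incidence for an outcome over 12 months. The Data analysis section plans logistic mixed models for repeated categorical outcomes, so the percentages above are not the power of that exact analysis. The model's constant rate and perfect detection are simplifications; imperfect detection would lower power further.

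A reader might also infer that a child who is in hospital or has died on a visit day becomes a missing value and is imputed. The documents do not support this. The Data analysis section provides multiple imputation for missing observations but does not say that deaths or admissions are treated as missing, and such handling is commonly left to the analysis plan.

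**Conclusion.** The point holds in conditional form, with medium confidence. The sample size arithmetic is correct. The fault is that the outcome and its power refer to 12-month incidence, while the case-finding described would observe prevalence on visit days.

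Unless interval episodes are also recorded, and if 0.50 and 0.30 are true cumulative risks, power in a simple ever/never comparison is about 14% to 44% for signs lasting 7 to 30 days. The direction holds for any duration well below three months; the exact figure does not, because duration is assumed.

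A reader might conclude that the observed control proportion will certainly be far below 0.50 and that the 80% power is simply absent. That goes further than the documents allow, since the additional file, the duration of signs and the case-finding behind the 0.50 are all unknown.

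**What to change.** Align the outcome, the case-finding and the power statement in one of two ways.

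- **(a) Keep examination as the source.** Name the primary outcome 'pneumonia at quarterly examination', withdraw the 80% power claim for 0.50 versus 0.30, and restate power for the proportions that quarterly examination can detect over a stated range of durations. This costs only rewriting, but it narrows the question and makes low power visible. Restoring 80% by sample size alone, under formula (i) and with 25% dropout, would take about 1,288, 655 or 319 children per group at 7, 14 or 30 days, against 124 planned.
- **(b) Keep 12-month incidence.** State that episodes since the last visit are recorded at the existing 3-monthly visits, say how such an episode qualifies as a case, and restate power for that case-finding. If Additional file 1 already contains such items, the change is to cite them in the definition. Otherwise it means a few more form items; retrieving clinic or hospital records would cost more. The downside is bias: the Randomisation section blinds only the data analyst, so caregiver report is unblinded and may be misclassified differently by arm. Examination-confirmed cases should therefore be a separately reported outcome.

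Because recruitment is described as ongoing, the change should be dated and made before anyone sees pneumonia data by arm.
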